## Abstract

**Background:**

Sleep disruptions are common during pregnancy and associated with increased risk of adverse maternal outcomes such as preeclampsia, gestational diabetes, prolonged labor, and cesarean birth. Given the morbidity associated with poor sleep, cost-effective approaches to improving sleep that can be disseminated in community or clinical settings are needed. Personal health monitor (PHM) devices offer an opportunity to promote behavior change, but their acceptability and efficacy at improving sleep in pregnant women are unknown.

**Objective:**

The goal of the paper is to describe the protocol for an ongoing pilot randomized controlled trial that aims to establish the feasibility, acceptability, and preliminary efficacy of using a PHM device (Shine 2, Misfit) to promote sleep during pregnancy.

**Methods:**

The proposed pilot study is a 12-week, parallel arm, randomized controlled trial. Pregnant women, at 24 weeks gestation, will be randomized at a 1:1 ratio to a 12-week sleep education plus PHM device group or a sleep education alone comparison group. The primary outcomes will be measures of feasibility (ie, recruitment, enrollment, adherence) and acceptability (ie, participant satisfaction). The secondary outcomes will be self-reported sleep quality and duration, excessive daytime sleepiness, fatigue, and depressive symptoms.

**Results:**

Recruitment for this study began in September 2017 and ended in March 2018. Data collection for the primary and secondary aims was completed in August 2018. We anticipate that the data analysis for primary and secondary aims will be completed by December 2019. The results from this trial will inform the development of a larger National Institutes of Health grant application to test the efficacy of an enhanced version of the sleep intervention that we plan to submit in the year 2020.

**Conclusions:**

This study will be the first to apply a PHM device as a tool for promoting self-management of sleep among pregnant women. PHM devices have the potential to facilitate behavioral interventions because they include theory-driven, self-regulatory techniques such as behavioral self-monitoring. The results of the study will inform the development of a sleep health intervention for pregnant women.

**Trial Registration:**

ClinicalTrials.gov NCT03783663; https://clinicaltrials.gov/ct2/show/NCT03783663 (Archived by WebCite at http://www.webcitation.org/779Ou8hon)

**International Registered Report Identifier (IRRID):**

DERR1-10.2196/12455

## Introduction

Sleep disruptions are common during pregnancy [1] and are associated with an increased risk of adverse maternal/fetal outcomes such as hyperglycemia [2,3], gestational diabetes [4], preeclampsia [5], cesarean delivery [6], longer labor [7], and delivering a low birthweight infant [8]. Additionally, women with poor sleep in pregnancy experience increased depressive symptoms during pregnancy [9] and postpartum depression [10], which increase their risk of depression later in life [11].

While sleep disruptions among pregnant women are often due to physical (eg, pain, nocturia, growing fetus) and hormonal changes [12], lifestyle factors such as sleep hygiene (ie, behavioral and environmental habits that promote or disrupt sleep) also contribute to sleep disruptions. For example, in a convenience sample of 197 pregnant women in their third trimester of pregnancy in Taiwan, poor sleepers were shown to have worse sleep hygiene than good sleepers [13]. Moreover, other health behaviors, such as physical activity and diet, are associated with better sleep duration in pregnancy [14-17]. These studies demonstrate that modifiable factors contribute to sleep disruptions during pregnancy, suggesting that interventions could make a positive impact on sleep in this group. A review of seven nonpharmacological (eg, acupuncture, physical activity, massage) sleep interventions during pregnancy showed trends of improving sleep; however, the studies have generally been of low quality and none focused on sleep hygiene [18]. Given the scarcity of effective approaches to promote sleep among pregnant women, there is a need to develop interventions that can be easily disseminated in community or clinical settings.

Personal health monitors (PHMs) have grown in popularity, with an estimated 1 in 8 consumers now owning a PHM [19]. The popularity of PHM use may provide an opportunity to promote positive health behaviors, such as sleep health, on a large scale. Many PHM devices include theory-driven behavior change techniques such as self-monitoring, goal setting, review of behavioral goals, rewards, and facilitation of comparisons with peers [20]. Several researchers have incorporated the use of PHMs into standard interventions to promote physical activity and weight loss [21-26]. However, there is limited evidence on the efficacy of wearable devices to promote sleep.

Here we describe the protocol for an ongoing pilot randomized controlled trial [NCT03783663] that aims to establish the feasibility, acceptability, and preliminary efficacy of using a PHM device (Shine 2, Misfit) to promote sleep during pregnancy. Specifically, the primary aim of the study will be to (1) establish the feasibility and acceptability of conducting a 12-week intervention for sleep self-management among pregnant women using a PHM device and (2) determine the feasibility of collecting data on sleep and physical activity using a PHM device. The secondary aim will be to determine the preliminary efficacy of the trial on improving self-reported sleep quality and nocturnal sleep duration and decreasing sleep disturbances, excessive daytime sleepiness, fatigue, and depressive symptoms.

## Methods

### Study Design

This pilot study is a 12-week, parallel arm, randomized controlled trial. Participants will be randomized at a 1:1 ratio to a 12-week sleep education plus PHM device group or a sleep education alone comparison group at approximately 24 weeks gestation of pregnancy (Figure 1). This time period was chosen to capture data during the third trimester of pregnancy when sleep may worsen [1] while allowing sufficient time for study completion prior to birth. We will use blocked randomization to ensure equal group size due to the small pilot sample size. The study has been approved by the institutional review board of the University of Massachusetts Amherst. All participants will be required to provide informed written consent prior to enrollment.

**Figure 1 figure1:**
[figure not shown]
Participant flowchart.

### Procedures

At the time of recruitment (t_0_) (14 to 24 weeks gestation), participants will complete a screening survey to determine their eligibility. At 24 weeks gestation (t_1_), eligible participants will enroll in the study and complete a baseline survey to assess demographic characteristics and secondary outcome measures. Both researchers and participants will be blinded to group assignment at the baseline assessment and during the educational intervention. All participants will receive an individual 30-minute educational intervention on sleep hygiene during pregnancy delivered by a study registered nurse at enrollment. The focus on the sleep education will be to provide tips on how to achieve a better night’s sleep during pregnancy such as managing pregnancy weight gain with aerobic activity and keeping a consistent schedule. Participants will also receive a sleep hygiene brochure, adapted from a Massachusetts Lung and Allergy sleep clinic sleep hygiene brochure to include information specific to pregnancy. We piloted the development of the brochure through an online survey that asked about the usefulness of the information and overall aesthetics. We used similar recruitment approaches (ie, Facebook) and eligibility criteria to identify women in the brochure development pilot as will be used for the pilot intervention to ensure the feedback is appropriate for the target population. Based on the participant feedback, we made modifications to the brochure’s graphical design; the information content was deemed useful. After completing the baseline survey and sleep hygiene education, participants and researchers will be unblinded to the group assignment (t_2_). Assignments will be made prior to the start of recruitment by randomizing study identification (ID) numbers into intervention or control group using Web-based randomization software [27]. The results of the randomization process will be placed into individually sealed envelopes labeled with study ID numbers. At t_2_, the study nurse will open the envelope for the ID number assigned to the participant and reveal group assignment. Those in the intervention group will then receive the intervention.

At 36 weeks gestation (t_3_), all participants will complete an in-person follow-up survey to assess the same secondary outcome measures as at t_1_. Participants will also complete a brief qualitative interview to determine their satisfaction with the sleep hygiene education and, for those in the intervention group, the self-monitoring intervention. Participants will complete a final follow-up phone survey approximately 2 to 4 weeks after delivery (t_4_).

### Study Population

We will recruit pregnant women who reside within approximately 50 miles of the University of Massachusetts Amherst campus. To be eligible to participate in the study, at the time of recruitment (t_0_) women must (1) be aged 18 years or older, (2) be 14 to <24 completed weeks gestation, (3) have no known maternal or fetal complications, (4) have a mobile phone compatible with the study PHM device, (5) have internet access, (6) be English speaking, and (7) be receiving prenatal care. We will exclude women with preexisting diabetes mellitus, hypertension, or a diagnosed sleep disorder, as some research demonstrated that associations between gestational diabetes and hypertension and a preexisting diagnosed sleep disorder would bias study results [28]. For the purpose of establishing feasibility and acceptability of recruitment and implementing the intervention, the sample size goal is 10 women per group. To account for attrition, we will oversample by 20%, recruiting 12 women per group.

Recruitment will be conducted through advertisements posted (1) at local commercial and community centers frequented by pregnant women in western MA, (2) at a women’s health clinic in western MA, (3) at community centers with diverse memberships such as churches, and (4) on Facebook and Craigslist. The study nurse will also recruit participants in person in the waiting room of the women’s health clinics at the University of Massachusetts Medical Center. During screening/enrollment, we will document the source of recruitment for each participant.

### Intervention

#### Conceptual Framework

The conceptual framework for the intervention is based on a meta-regression of lifestyle (ie, healthy eating and physical activity) interventions among adults by Michie et al [29]. The authors found that lifestyle interventions incorporating self-monitoring and one other self-regulatory technique derived from control theory (ie, intention formation, setting goals, feedback on performance, review of behavioral goals) were more effective at promoting behavior change (pooled effect size = 0.38; 95% CI 0.27 to 0.49) than studies not including these techniques (pooled effect size = 0.27; 95% CI 0.21 to 0.34). Likewise, in their systematic review and meta-analysis on the efficacy of postpartum physical activity interventions, Gilinsky et al [30] found that efficacious interventions were twice as likely to include self-monitoring than nonefficacious interventions. Guided by this conceptual framework, the sleep intervention will include (1) behavioral self-monitoring (using the Shine 2), (2) goal setting (30-minute sleep education session), (3) feedback on performance (Shine 2), and (4) review of behavioral goals (Shine 2).

#### Instrumentation

The intervention group will be given a Shine 2 to monitor sleep throughout the 12-week intervention period. The Shine 2 is a triaxial accelerometer that can be worn on the wrist, waist, neck, pocket, or shoe. The Shine 2 measures steps, intensity, energy expenditure, distance traveled, and sleep duration using a proprietary algorithm. The Shine 2 was selected because it can be worn continuously (even during water-based activities), does not require charging (approximate 6-month battery life), and does not require participants to set the device to sleep mode in order to capture sleep patterns, features that may improve adherence to the intervention. The Shine 2 has been shown to provide equivalent estimates of total sleep time as in-lab polysomnography (*r*=.87), the gold standard for sleep assessment [31].

Participants will be instructed to wear the device on the wrist, which is better for capturing sleep than the other wear locations. Participants will be instructed on how to self-monitor total sleep time and select a goal for that behavior. Figures 2 and 3 show examples of the feedback participants receive on their sleep relative to their self-selected sleep goals. Further, participants will view feedback on their sleep time daily on the Shine 2 mobile phone app, which they can use to monitor their progress toward achieving their behavioral goals. The Shine 2 syncs with iPhone, Android, and Windows phones. Instructions for syncing the Shine 2s to phones will be included in an instructional brochure designed by the study team. Study-specific Gmail accounts and passwords will be created for each study ID so we can access their sleep and physical activity data. Participants will download the Shine 2 app to their mobile phone and create a Shine 2 account using the assigned study Gmail address. Participants will also download the IFTTT app, a free platform that facilitates downloading and sharing data from a PHM [32]. Participants will activate two IFTTT applets that connect Shine 2 with a Google spreadsheet in Google Drive: (1) “Save your Misfit Shine 2 sleep logs to a Google spreadsheet” and (2) “Document your daily activity summaries.” The applets will automatically download the Shine 2 data for sleep daily to the participant’s study Gmail account, making it viewable by the research team. This will allow the research team to view participant progress toward meeting their sleep goals. To enhance data security, the study Gmail account will be used only to collect the Shine 2 data (ie, will not be used for email or other purposes), and the Google Drive accounts will be accessed only by study team members using computers that are password-protected and encrypted. Further, no identifying personal information will be contained within the Gmail account. At the end of the study, participants will be instructed to change their email addresses and passwords in their Shine 2 account to a personal email and password so investigators will no longer have access to their Shine 2 accounts. Once all Shine 2 data have been extracted from the study Google Drive accounts, the accounts will be closed. A team member will conduct follow-up calls to intervention participants one week after enrollment and then monthly to address any issues with using the study device and to answer questions.

**Figure 2 figure2:**
[figure not shown]
Misfit Shine 2 dashboard displaying the previous night’s sleep duration and self-selected sleep goal.

**Figure 3 figure3:**
[figure not shown]
Misfit Shine 2 dashboard displaying weekly trend of sleep duration and self-selected sleep goal.

#### Intervention Fidelity

The sleep hygiene education session will be provided to both groups by the study nurse. To increase fidelity, a specific protocol for delivering the education to each group will be developed by the principal investigator, and the study nurse will be trained by the principal investigator on the protocol. The delivery of education to study participants will be audio recorded with a digital recorder. The principal investigator will listen to each recording to ensure that participants are receiving the same information per the protocol. In the event that deviation from the protocol is noted, the principal investigator and study nurse will meet to review and retrain on the protocol.

### Primary Outcomes: Intervention, Feasibility, and Acceptability

Table 1 describes the schedule of study assessments for primary and secondary outcomes measures.

#### Recruitment

At t_0_, participants will be asked how they learned about the study (eg, Facebook, community center), with follow-up questions to gather specific details as necessary. The frequency and percentage of participants recruited by each recruitment method will be calculated. We will present descriptive data on the number screened, eligible, and randomized from each source.

#### Retention

Retention may be a challenge due to the longitudinal nature of the study. Each participant will be asked to provide multiple contact methods. Increasing incentives will be built into the study at each data collection time point ($20, $30, and $40 gift cards) to encourage retention for both the intervention and control groups. Participants in the intervention arm will keep the Shine 2 device at the study end. Participants in the control arm will be offered a Shine 2 at the study end. The ability to successfully contact participants, deliver the intervention, and collect data at each time point will be recorded to calculate the percentage of participants retained.

To evaluate participant retention with the intervention protocol, the study team will take two actions. First, we will track sleep data weekly for each participant by viewing their sleep log in the study Gmail account. Then, if a lack of data in the sleep log suggests that the participants are not wearing the monitor daily, we will call the participants to find out why they are not using the device, help them problem solve any issues, and encourage them to continue with study adherence.

**Table 1 table1:** Schedule of study assessments for primary and secondary outcomes.

Characteristics			Assessment			
			Screening/enrollment	Baseline	Active intervention	
			t_0_	t_1_	t_2_	t_3_
**Primary outcomes**						
	**Recruitment/enrollment**					
		Eligibility screen	X			
		Informed consent	X			
		Allocation			X	
		Retention				X
		Participant satisfaction				X
**Secondary outcomes**						
	Sleep quality and duration			X		X
	Sleep disturbances			X		X
	Excessive daytime sleepiness			X		X
	Fatigue			X		X
	Depressive symptoms			X		X

#### Participant Satisfaction

Participants in both groups will be asked to complete a semistructured interview at the 12-week follow-up data collection meeting (t_3_). The interview questions will ask participants about their sleep, barriers and facilitators of sleep, and whether the brief sleep counseling was helpful. Women in the intervention group will additionally be asked about their experience wearing the Shine 2, their likes, dislikes, and whether they believe it would be helpful to other pregnant women.

### Secondary Outcomes

#### Sleep Quality and Duration

The Pittsburgh Sleep Quality Index (PSQI) will be used to measure sleep quality and duration [33]. The PSQI is a 19-item scale measuring perceived sleep quality and disturbance over the past month. For this study, the PSQI will be adapted to measure perceived sleep quality over the past week. The PSQI has been used in numerous studies with pregnant women and has been validated for pregnant women using confirmatory factor analysis and has a reliability of .74 [34]. Scores ≥5 will be considered indicative of poor sleep.

#### Sleep Disturbances

The PROMIS Short Form v1.0–Sleep Disturbance 6a will be used to measure sleep disturbances [35]. This validated 6-item scale measures individual perceptions of sleep quality and disturbance in the past seven days using a 5-point Likert scale. It is scored by summing responses for all items (two are reverse scored); higher scores indicate higher sleep disturbance.

#### Excessive Daytime Sleepiness

The Epworth Sleepiness Scale is an 8-item measure of daytime sleepiness [36]. It has been validated for measuring symptoms of daytime sleepiness in pregnant women using principal components and confirmatory factor analysis and has a reliability coefficient of .75 [37]. Higher cumulative scores indicate higher sleepiness.

#### Fatigue

The PROMIS Fatigue Short Form 4a will be used to measure fatigue. This 4-item scale measures fatigue in the past seven days with a 5-point Likert scale [38]. Responses for all items are summed; higher scores indicate higher fatigue symptoms.

#### Depressive Symptoms

Two scales will be used to measure depressive symptoms in the past seven days. The PROMIS Depression Short Form 6a is a 6-item scale scored by summing responses for all items, with higher scores indicating higher depressive symptoms. It has been validated for use with several chronic illnesses [39]. Although this scale has not been validated in pregnant women, it is a common data element measurement tool that is supported by the National Institutes of Heath. This will allow us to upload deidentified data gathered with this tool to the National Institute for Nursing Research Common Data Elements Repository. We will additionally measure sleep using the Edinburgh Postnatal Depression Scale, a 10-item scale designed to detect depressive symptoms in postpartum women [40], with support for detection of depressive symptoms in pregnancy [41]. Scores range from 0 to 30; a higher score indicates higher depressive symptoms. We will use scores >12 to indicate depressive symptoms.

### Covariates

We will collect information on demographic characteristics and eating habits. Demographic characteristics will include age, ethnic background, racial background, relationship status, level of education, employment status, hours worked per week, and income level. Eating habits will be measured using the Dietary Targets Monitor, a 9-item self-report questionnaire assessing consumption of fruits, vegetables, starchy foods, and other types of foods such as meat and fish [42]. Recommended standard portion for each group will be used to calculate daily, weekly, and monthly consumptions of different foods [42].

### Data Analysis

We will use descriptive statistics to determine the feasibility and acceptability of the pilot intervention. Specifically, we describe recruitment and dropout rates in each group and noncompliance with the intervention among the intervention group only. To assess noncompliance we will use data from the IFTTT applet to determine the proportion of days the monitor was worn during the study period. High compliance will be defined as wearing the monitor at least 80% of days during the study period.

Qualitative methods will be used to determine the acceptability of the intervention, using a qualitative descriptive design [43,44]. The audio recorded interviews will be organized using NVivo 11 (QSR International Inc) software. Recordings will be professionally transcribed verbatim, and transcripts will be checked for accuracy. Descriptive coding will be used to identify and link comparable content and categorize data at a basic level [43]. For further analysis of descriptive codes, content analysis will be used to describe patterns and summarize findings in the data [44]. Memos will be written throughout the analytic process to capture the analysis process and the researchers’ responses to the data. Trustworthiness will be determined through peer debriefing between the research assistant and the principal investigator and the audit trial of documentation of the analysis, including coding, memos, and findings.

To examine the preliminary efficacy of the intervention, all secondary outcome variables will be modeled as continuous outcomes. We will compare baseline characteristics of the intervention groups to ensure randomization was successful. We will present the mean and standard deviation or median and interquartile range for each secondary outcome at baseline and postintervention. A paired *t* test will be used to compare baseline and postintervention means separately in each group. A Student *t* test will then compare the change in each measure between the two intervention groups. Finally, we will calculate within and between-group effect sizes using Cohen d (M_ΔI_ – M_ΔC_ / SD_pooled I and C;_ M_t2_ – M_t3_ / SD_pooled t2 and t3_).

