In addition to recruitment, participant adherence is another critical challenge this feasibility study will help inform. Since previous studies did not use a PHM device specifically to monitor sleep, we would like to first address if pregnant women will wear them for this purpose. Through the IFTTT app, we will be able to identify when the monitor is not worn and elicit feedback from participants on any barriers to wearing the device. If specific benchmarks for retention are not met (>80%), we will refine our current approach (eg, incentive, engagement strategies) to address any challenges that exist.

Last, this feasibility trial will provide important information about the implementation of the intervention. The intervention was meant to be a low-contact intervention to be consistent with the limited time resources in a clinic setting. Through the participant satisfaction interview, we will determine whether the initial counseling session and sleep brochure address challenges specific to pregnant women. Concerning the instruments for the intervention (Shine 2), we will learn if there are specific features participants liked or did not like about the device and the extent to which participants used the device to self-monitor their sleep. Identifying specific features will allow us to be responsive to rapid changes in technology, steering us to select a device that contains features participants find particularly helpful. More generally, we will learn if wearing the PMH device serves as a motivator to participants to monitor their sleep more closely and identify behaviors affecting their sleep.

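### Days worn are read only from IFTTT records, so the wear figure is a lower bound that mixes data loss with non-wear, and primary aim 2 has no named outcome.

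*Protocol article*

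**What the plan says.** The Abstract (Methods) defines the primary outcomes to include "measures of feasibility (ie, recruitment, enrollment, adherence". The Introduction sets two primary aims. The second is to "determine the feasibility of collecting data on sleep and physical activity using a PHM device", and Principal Findings in the Discussion repeats it.

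Under Data Analysis, for noncompliance, "we will use data from the IFTTT applet to determine the proportion of days the monitor was worn". The cut-off follows: "High compliance will be defined as wearing the monitor at least 80% of days during the study period". Principal Findings states the inference directly: "Through the IFTTT app, we will be able to identify when the monitor is not worn".

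Instrumentation describes the route of the data: "Participants will activate two IFTTT applets that connect Shine 2 with a Google spreadsheet in Google Drive". One applet carries sleep logs and the other daily activity summaries. Retention plans a weekly look at the sleep log and adds that "if a lack of data in the sleep log suggests that the participants are not wearing the monitor daily, we will call the participants" to ask why and help. Instrumentation also plans support calls at one week and then monthly. Participant Satisfaction plans an exit interview about wearing the device.

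**The concern.** An IFTTT record shows that a row arrived. Its absence does not show that the device was off the wrist. Under Instrumentation, a row also needs the device to sync with the phone, the account to be linked, the applet to stay active and the Google sheet to be written. If any step after the app fails, a worn day leaves the same empty row as an unworn one.

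Primary aim 2 asks whether this kind of data collection works. Scoring adherence from the same records takes for granted that it does. The feasibility quantities listed in Data Analysis are recruitment, dropout and noncompliance, and none of them measures data capture. The activity records are collected but enter no stated analysis.

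The pilot is meant to shape a larger trial. Women who do not wear the device and records that go missing call for different remedies, and one combined figure does not say which problem occurred.

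**Working it through.** **Inputs from the article.** High-compliance cut-off 80% of days (Data Analysis). Twelve-week intervention period (Instrumentation). Target of 10 women per group, raised by 20% to 12 (Study Population): 10 × 1.20 = 12, which reproduces and is used here only for the arm size.

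**Assumptions.** The study period for wear is 12 × 7 = 84 days; Data Analysis does not state it in days. An unworn day yields no record that is counted as wear. True wear *w* and link yield *y* (the share of worn days whose record arrives) are not given, so ranges are shown.

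**Threshold.** 0.80 × 84 = 67.2, so 68 recorded days are needed and at most 16 may be missing. With 17 records lost, a daily wearer has 67/84 = 79.8% and is not classed as highly compliant.

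**Direction.** Recorded wear = *w* × *y*. Since *y* cannot exceed 1, recorded wear cannot exceed true wear.

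**Break-even.** Recorded wear falls below 80% once the share of worn days lost exceeds 1 − 0.80/*w*. That is 20.0% at *w* = 100%, 15.8% at 95%, 11.1% at 90% and 5.9% at 85%.

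**Illustration at an assumed *w* = 0.90.** With X ~ Binomial(84, *w* × *y*), the chance of being classed as highly compliant is P(X ≥ 68):

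| Link yield *y* | Recorded wear | P(X ≥ 68) |
|---|---|---|
| 1.00 | 0.900 | 0.996 |
| 0.95 | 0.855 | 0.906 |
| 0.90 | 0.810 | 0.571 |
| 0.85 | 0.765 | 0.204 |
| 0.80 | 0.720 | 0.040 |

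These probabilities treat days as independent with constant yield. An inactive applet or unlinked account would more likely lose a run of days in a few women.

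**A run of lost days.** Suppose a woman wears the device on 80 days and 14 of those records are lost downstream. The planned measure gives (80 − 14)/84 = 66/84 = 78.6%. Counting the 14 as worn gives 80/84 = 95.2%. Record yield among worn days is 66/80 = 82.5%, which is information for aim 2.

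**Arm level.** If every woman were truly compliant and three were misclassified, the share would be 7/10 = 70% or 9/12 = 75%. Principal Findings expects at least 80% of women to wear the device daily.

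**Where aim 2 could be answered.** The Primary Outcomes sections cover recruitment, retention and satisfaction. The primary rows of Table 1 hold screening, consent, allocation, retention and satisfaction. Data Analysis lists recruitment, dropout and noncompliance. No device-data item appears in any of them.

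**The case against.** The rule that a day without a record counts as not worn is nowhere written out. Data Analysis names only the source, Retention says that missing data suggest non-wear and prompt a call, and the statement that IFTTT identifies non-wear is in the Discussion. The definition of a valid wear day may sit in a fuller document. This stands as a caution: the rule is inferred from Data Analysis read with Principal Findings. The article nevertheless fixes IFTTT as the wear source and offers no other reading.

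The calls and exit interviews can reveal why records are missing, and with about 12 women reported descriptively that may explain a low figure. This also stands in part. However, nothing says that the reason found changes how a day is counted.

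Not every link failure is measurement error. If the device does not sync with the phone, the woman does not receive the app feedback that is part of the intervention, so counting that day as full adherence would overstate exposure. This stands, and the fix keeps such days apart.

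A reader might infer that the primary result is shown to be materially biased. The article does not support that: it gives no failure rate, and the loss could be small. A reader might also infer that aim 2 cannot be concluded at all. That goes too far, because record counts can be taken from the spreadsheets and the calls and interviews add partial information. What is missing is a named outcome.

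**Conclusion.** The concern holds in this form. Recorded wear is a lower bound for true wear, because records lost after the app cannot be told from non-wear in the only source named, and primary aim 2 has no named outcome. The direction rests on the assumption that unworn days produce no counted record. The size is unknown. The 17-record example assumes 84 days, and the probabilities further assume 90% true wear, the yields shown and independent days. They show how sensitive the 80% label is and do not estimate the loss in this trial.

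The two explanations for low recorded wear lead to different changes in the larger trial, though not opposite ones, and no hypothesis test or stopping rule rests on the figure. The matter is worth correcting because it touches a primary measure and a primary aim, and it can be repaired within a descriptive analysis.

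**What to change.** In Data Analysis:

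- Label the IFTTT figure 'days with data received' and present it as a lower bound for wear.
- Count a gap day as worn where call notes, or Shine 2 account data that are still accessible, show that the device was worn and synced but the record was lost downstream.
- Show device-to-phone sync failures as a separate category.
- Show gap days that cannot be classified as a range, counted first as all not worn and then as all worn.
- State the number of days in the denominator.

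For primary aim 2, report the proportion of days with records received, separately for the sleep and activity applets, and add this outcome to Table 1. Where the classification allows, also give it among days known to be worn and synced, so that it is not merely the recorded-wear figure under another name.

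The cost is a few lines of wording and a few hours of record review for about 12 women. Some gap days will remain unclassifiable. Data collection ended in August 2018, women were to change their logins at study end and the Google accounts were to be closed after extraction, so account checks may no longer be possible. The article also does not say that call reasons were noted by day. If neither source can be used, the relabelling, the lower-bound statement, the range and the yield per applet can still be done from the extracted records.
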